# SYNOPSIS

| Study Title | **A pilot study of adjunctive aspirin for the treatment of HIV negative adults with tuberculous meningitis** |
| --- | --- |
| Internal ref. no. | 23TB |
| Clinical Phase | Phase II |
| Trial Design | Double blind, 1:1:1 randomized placebo controlled trial |
| Trial Participants | Adults with tuberculous meningitis |
| Planned Sample Size | 120 patients |
| Follow-up duration | 240 days |
| Planned Enrolment Period | September 2014 to December 2016 |
| Primary Objective | To generate pilot data on the safety and efficacy of 81mg daily and 1000mg daily dose adjunctive aspirin. |
| Secondary Objectives | To determine whether host genotype influences any of the above effects  To determine whether innate host macrophage antimicrobial activity influences outcome  To assess the plasma pharmacokinetics of aspirin |
| Primary Endpoint | Primary safety endpoint: Clinically significant upper gastro-intestinal or cerebral bleeding by 60 days  Primary efficacy endpoint: New MRI-proven brain infarction or death by 60 days |
| Secondary Endpoints | Time to death during 240 days  Neurological disability by 60 days and 240 days  Duration of hospital stay  Grade 3&4 and serious adverse events by 60 days  The proportion of patients with MRI-proven infarction by day 240  Antimicrobial activity of peripheral blood monocyte/macrophages on day 30 and 60 compared to baseline  Concentration-time profile of salicylic acid including exposure, peak levels, half-life, elimination clearance and volume distribution |
| Investigational Medicinal Products | Aspirin and placebo |
| Form | Tablet |
| Dose | 81mg,1000mg or placebo daily for 60 days |
| Route | Oral/nasogastric tube (if unable to swallow safely) |

#

# ABBREVIATIONS

| AE | Adverse event |
| --- | --- |
| ATC | Anti-tuberculosis chemotherapy |
| COX | Cyclooxygenase |
| CRF | Case Report Form |
| CSF | Cerebrospinal fluid |
| DSMB | Data Safety Monitoring Board |
| GCP | Good Clinical Practice |
| HIV | Human Immunodeficiency Virus |
| HTD | Hospital for Tropical Diseases, Ho Chi Minh City, Vietnam |
| ICF | Informed Consent Form |
| ICH | International Conference of Harmonisation |
| IMP | Investigational Medicinal Product |
| LTA4H | Leukotriene A4 hydrolase |
| MRI | Magnetic resonance imaging |
| NSAID | Non-steroidal anti-inflammatory drug |
| OUCRU | Oxford University Clinical Research Unit |
| OXTREC | Oxford Tropical Research Ethics Committee |
| PG | Prostaglandins |
| PI | Principal Investigator |
| PV | Protocol Violation |
| SAE | Serious Adverse Event |
| TBM | Tuberculous meningitis |
| TMF | Trial Master File |
| TXA2 | Thromboxane A2 |
| USAE | Unexpected Serious Adverse Event |

# BACKGROUND AND RATIONALE

Tuberculous meningitis (TBM) is the most devastating form of tuberculosis, killing or maiming around half of all sufferers [^1^](#_ENREF_1). There are three broad approaches to improving outcome: earlier diagnosis and treatment with anti-tuberculosis chemotherapy (ATC), enhancing anti-microbial killing by optimising or improving standard ATC, and controlling the intra-cerebral inflammatory response. Studies performed nearly a decade ago at the Hospital for Tropical Diseases (HTD), Ho Chi Minh City, demonstrated how simple clinical and laboratory methods assist in early TBM diagnosis [^2-4^](#_ENREF_2) and that adjunctive corticosteroids reduce mortality from the disease [^5^](#_ENREF_5). The current HTD/OUCRU trial (05TB) examines the hypothesis that enhanced early bacterial killing with high-dose rifampicin and levofloxacin will increase survival from TBM [^6^](#_ENREF_6). The trial completed recruitment of 817 adults with TBM in June 2014.

This pilot study returns to the long-standing hypothesis that outcome from TBM can be improved by control of the intra-cerebral inflammatory response. Our previous randomised controlled trial of adjunctive dexamethasone in 545 adults with TBM found dexamethasone increased survival but had no impact on neurological disability [^5^](#_ENREF_5). Indeed, 5-year follow-up of trial patients found dexamethasone’s impact on survival was lost after around 2 years, primarily because of the deaths of the higher proportion of severely disabled patients in the dexamethasone treatment arm[^7^](#_ENREF_7). There is, therefore, an urgent need to explore ways to prevent the neurological sequelae of TBM which complement the effect of dexamethasone on survival. We hypothesise that aspirin will reduce neurological sequalae from TBM by enhancing the resolution of intra-cerebral inflammation and by preventing intra-vascular thrombosis and brain infarction.

***Mechanism of TBM-related cerebral infarction***

Cerebral infarction is the commonest cause of irreversible neurological damage in patients with TBM, although the pathological mechanisms by which it occurs are poorly understood [^8^](#_ENREF_8). Post mortem studies performed in the late 19th century found that infarcts were most frequently seen in relation to small or medium-sized vessels occluded by intimal infiltration and/or proliferation [^9^](#_ENREF_9). Seminal autopsy and animal studies performed in the early 20^th^ century by Rich and McCordock reported vessel wall inflammation was more likely to have spread from the adventitia inwards, reflecting the severity of the surrounding subarachnoid inflammatory exudates [^10^](#_ENREF_10). In keeping with these observations, TBM-related infarcts are most commonly located in the territories of the proximal middle cerebral artery and the medial lenticulostriate and thalamoperforating vessels, where the basal meningeal inflammatory exudate is at its most intense [^8^](#_ENREF_8).

The role of vessel thrombosis in causing TBM-related cerebral infarcts is controversial. When specifically sought in autopsy TBM brains, some investigators have either failed to find arterial thrombosis, or found it to be uncommon [^11^](#_ENREF_11). Others assert that thrombosis is common, especially when there is an associated tuberculous vasculitis[^12^](#_ENREF_12). It seems most likely that TBM-related infarcts are caused by a variable combination of vasospasm, intimal proliferation and thrombosis [^8^](#_ENREF_8).

***Aspirin mechanism of action***

There are cogent reasons to believe that aspirin may reduce TBM-related infarcts and consequent neurological morbidity, when corticosteroids do not. Aspirin (acetylsalicylic acid) is the prototypical non-steroidal anti-inflammatory drug (NSAID), but one with unique anti-inflammatory and anti-thrombotic properties [^13^](#_ENREF_13). It acts by irreversibly inhibiting the cyclooxygenase (COX) pathway of arachidonic acid metabolism and the production of prostaglandins (PG). Aspirin is licenced in the United Kingdom at low dose (75-150mg) for the prevention of cerebrovascular disease (myocardial infarction and stroke, for example) and at higher dose (up to 4 grams daily) for the treatment of inflammatory conditions (e.g. arthritis and rheumatic fever).

Its anti-inflammatory effects are thought to occur at high dose (≥ 1 gram daily) and are produced by the inhibition of pro-inflammatory prostaglandins (e.g. PGE2, PGF2α and PGD2) as well as the unstable prostanoids, prostacyclin and thromboxane A2 (TXA2) [^13^](#_ENREF_13). Low dose aspirin (75-150mg) has less inhibitory effect on the pro-inflammatory prostaglandins, but still causes clinically significant inhibition of TXA2 and platelet aggregation. Until recently, it was the inhibitory effect on platelets and thrombus formation that was thought to explain aspirin’s well-documented reduction in the risk of death from stroke and myocardial infarction [^14^](#_ENREF_14). However, it is now appreciated that the beneficial effects of low dose aspirin may also stem from its ability to trigger the production of 15-epi-lipoxins, a class of molecules (alongside recently discovered resolvins, protectins and maresins) which actively promote resolution of inflammation[^15^](#_ENREF_15). The ‘pro-resolution’ properties of aspirin are not shared with any other NSAID and represents a potentially unique mode of action by which low-dose aspirin, alongside the prevention of thrombosis and stroke, might speed resolution of intra-cerebral inflammation and improve outcome from TBM.

***Clinical data supporting a role for aspirin in TBM treatment***

Two recent clinical studies suggest aspirin is safe when added to dexamethasone and may improve outcome from TBM. The first study randomised 118 Indian adults with TBM to standard anti-tuberculosis chemotherapy, with or without aspirin (150mg daily)[^16^](#_ENREF_16). The investigators hypothesised that aspirin would reduce the incidence of stroke and the primary endpoint was MRI-proven infarction by 3 months, with or without neurological deficit. By 3 months, MRI proven stroke occurred in 21 (33.3%) of all patients: 13 (43%) in the placebo arm and 8 (24%) in the aspirin group (P=0.18). Aspirin was associated with a significant reduction in mortality (43% versus 21.7%, P=0.02). The incidence of adverse events was not significantly different between the treatment groups and, in particular, there was no aspirin-associated gastro-intestinal bleeding reported. The results are hard to interpret, however, because of the variable use of prednisolone across the treatment arms. Prednisolone was given for severe disease at baseline, or if a patient’s condition worsened after the start of treatment. Any effect of aspirin, especially on mortality, is hard to disentangle from that of the corticosteroids.

A second study randomised 146 South African children with TBM to standard anti-tuberculosis chemotherapy plus placebo (n=50), low-dose aspirin (75mg/24 hours) (n=47), or high-dose aspirin (100mg/kg/24hours) (n=49) [^17^](#_ENREF_17). Aspirin has no significant impact on survival, but 9 children developed hemiplegia after the start of treatment and none of them received high-dose aspirin. Furthermore, the children in the high-dose aspirin group were significantly younger with more severe disease than the other treatment groups, yet their neurological outcomes were similar. Two children stopped aspirin early: one because of haematemesis and the other because of cerebral haemorrhage. Whether these patients received high or low dose aspirin was not reported.

***Leukotriene A4 hydrolase genetic polymorphisms and aspirin***

There is recent evidence from Vietnamese adults with TBM, that the balance of pro- and anti-inflammatory eicosanoids play an important role in determining susceptibility to TBM and the choice and impact of adjunctive inflammatory therapies. Using the zebra fish model of mycobacterial infection, Tobin and others found a polymorphism in the gene encoding the leukotriene A4 hydrolase (LTA4H) enzyme influenced tuberculosis susceptibility in both zebra fish and Vietnamese adults[^18^](#_ENREF_18). LTA4H controls the expression of pro- and anti-inflammatory eicosanoids, which in turn control the expression of the cytokine TNF-α (see **figure 1**).

**Figure 1. LTA4H genotype modulates susceptibility to mycobacterial infection**

*
[figure not shown]
*

Zebra fish at both poles of the inflammatory response (minor and major allele homozygotes) were unable to control mycobacterial replication within granulomas, whereas those fish with an intermediate inflammatory response (the heterozygotes) controlled the infection. The phenotype of the homozygous fish could be changed to that of the heterozygotes through the respective addition of pro-inflammatory leukotriene B4 (LTB4) or TNF-α to LTA4H low fish, or by inhibition of TNF-α in the LTA4H high fish by either aspirin or dexamethasone [^19^](#_ENREF_19). Furthermore, in Vietnamese adults recruited to the earlier dexamethasone trial, only major allele homozygous adults with the hyper-inflammatory phenotype benefited from dexamethasone (**Figure 2**). Indeed, dexamethasone treatment of those with a hypo-inflammatory phenotype appeared to be detrimental.

**Figure 2. LTA4H genotype influences survival from TBM in all patients (A), pre-treatment CSF leucocyte counts (B), and survival in those who did not (C) and did (D) receive adjunctive dexamethasone.**

[figure not shown]

These findings need replication in a different population, and such studies are currently underway at OUCRU, but they provide an elegant potential explanation for the previous failure to find the mechanism by which corticosteroids improve survival from TBM in Vietnamese adults. They also have important implications for the current pilot study and we will investigate the influence of LTA4H genotype on aspirin’s effect on CSF inflammation and clinical outcome.

**Macrophage antimicrobial activity and outcome from TBM**

We and others have shown that polymorphisms in genes responsible for the innate immune response to *Mycobacterium tuberculosis* influence both susceptibility to TBM and disease severity ^20, 21^. Macrophages are the key effector cells in the innate immune response to *M. tuberculosis*, but how variations in their innate antimicrobial activity influence outcome from TBM have not been previously investigated. In this study we will apply a panel of functional assays to directly measure the rates of acquisition of a variety of lysosomal characteristics known to impact microbial survival ^22, 23^. We will investigate whether these characteristics change through treatment and how they relate to the patient’s outcome.

**Why do we need this pilot study?**

There are several outstanding questions that need to be addressed by a pilot study before embarking on a large, definitive, randomised controlled trial of adjunctive aspirin for TBM. These are:

1. What is the safety and tolerability of 81mg and 1000mg dose aspirin when added to dexamethasone for the first 60 days of treatment of TBM?
2. Does aspirin at these doses reduce MRI-proven infarction and neurological sequelae or death?
3. Does 81 mg aspirin daily have the same anti-inflammatory effect as 1000 mg aspirin daily (assessed by measurement of CSF prostaglandins) and which dose is likely to be most effective?
4. How does host genotype (in particular, LTA4H genotype) influence the anti-inflammatory, anti-thrombotic, and clinical effects of aspirin?

# OBJECTIVES

## Primary Objective

To generate pilot data on the safety and efficacy of 81mg daily and 1000mg daily dose adjunctive aspirin compared to no aspirin.

## Secondary Objectives

To determine whether host genotype, including LTA4H genotype, influences any of the above therapeutic effects of aspirin

To determine whether innate host peripheral blood monocyte/macrophage antimicrobial activity influences outcome from TBM and varies through treatment

To assess the plasma pharmacokinetics of aspirin

# TRIAL DESIGN

.

## Summary of Trial Design

The study is a parallel group, double blind, randomised, placebo controlled trial of 60 days of placebo vs. 81mg daily dose vs. 1000mg daily dose aspirin for the treatment of HIV-uninfected adults with tuberculous meningitis (see trial schema in appendix A). Patients will be recruited at the Hospital for Tropical Diseases (HTD), Ho Chi Minh City, Vietnam and should not have had more than 2 days of anti-tuberculosis chemotherapy or have received aspirin or any other NSAID within 2 weeks of randomisation. They should be able to have an MRI of their brain within 5 days of randomization.

Once enrolled, patients will be followed for 60 days and followed up at 8months for final outcome. They will all receive standard anti-tuberculosis chemotherapy and adjunctive dexamethasone (for 6-8 weeks), according to respective National Tuberculosis Programme guidelines (see attached guidelines for Viet Nam with this protocol). Participants will be stratified by site and MRC disease severity grade, and randomised on entry to one of three arms (1:1:1 ratio): aspirin 81mg, aspirin 1000mg or placebo daily for 60 days. Patients will be in-patients for at least the first 14 days of study treatment enabling real-time active surveillance of any adverse events after which they will be discharged according to clinical care. Study drug and standard treatment may be continued while patients are followed as out-patients.

Lumbar puncture will be performed before the start of treatment and then repeated in all patients on day 30 and 60 as per normal clinical care. Blood draws for pharmacokinetic assessment will be done 5 times between days 1 and 14. Assessment of peripheral blood monocyte/macrophage antimicrobial activity will be made at baseline and on day 240.

Clinical assessments will be performed at enrolment and weekly between day 7 and discharge. Brain magnetic resonance imaging (MRI) will be performed at baseline, day 60 and 240. A final clinical assessment of neurological disability will be made at 240 days.

## Primary and Secondary Endpoints/Outcome Measures

The primary safety endpoint will be the occurrence of clinically significant upper-gastro-intestinal bleeding and any cerebral bleeding confirmed by brain imaging by 60 days from randomisation.

Clinically significant upper gastro-intestinal bleeding will be defined as any one of the following:

1. Vomiting fresh or changed blood of any volume
2. Melena
3. Unexplained drop in haemoglobin concentration of >2g/L
4. Greater than 5mls of fresh or changed blood aspirated from nasogastric tube

The primary efficacy endpoint will be any new MRI-proven brain infarction or death by 60 days. To assess this endpoint MRI will need to be taken at baseline and at 60 days from randomisation. The scans will be read by an independent neuroradiologist blind to the treatment allocation.

The secondary endpoints will be:

- Number of grade 3&4 and serious adverse events by day 60 from randomisation
- Time to death during 240 days from randomisation
- Duration of hospital stay
- Neurological disability (as assessed by the modified Rankin score and Glasgow outcome score) by days 60 and 240.
- Resolution of CSF inflammation by day 30 through measurement of CSF leucocytes, protein, glucose, cytokines (TNF-α, IL-1β, IL-8, IL-10, IFNγ) and eicosanoids (15-epi-Lipoxin, Lipoxin A4, LTB4, PGE2, TBXB2, PGD2).
- Antimicrobial activity of peripheral blood monocyte/macrophages on day 240 compared to baseline.
- The proportion of patients with MRI-proven infarction by day 240
- Concentration-time profile of salicylic acid including exposure, peak levels, half-life, elimination clearance and volume distribution

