### Subsequent Assessments

The outline of study assessments is provided in appendix B.

Follow-up clinical assessments should be made weekly until discharge from hospital. The assessments will include careful neurological examination and proactive surveillance for symptoms and signs of aspirin toxicity/adverse reactions (e.g. gastritis, tinnitus, gastrointestinal bleeding, renal impairment). All adverse events will be documented, followed and assessed for the likelihood of being related to aspirin.

A full blood count, and measurement of plasma urea, creatinine, electrolytes and stool microscopy for red blood cells will be taken on each clinical assessment day, day 30 and day 60 (5mls EDTA blood; 5mls clotted blood). Patients will have 20mls of heparinised blood taken at day 240 for assessment of the antimicrobial activity of peripheral blood monocytes/macrophages. Whole blood (2ml) will be obtained at 5 time points during the first 14 days of study treatment and analysed to assess the pharmacokinetic characteristics of aspirin.  Time points will be randomly assigned to a range of periods after drug dosing. A concentration-time profile of salicylic acid including exposure, peak levels, half-life, elimination clearance and volume distribution will be analysed.

Patients will have lumbar punctures on days 30 and 60, as per normal clinical care of patients with TBM in the hospital. 10mls of CSF should be taken when possible (as per normal care) and standard biochemical and microbiological tests performed (including mycobacterial smear and culture and GeneXpert MTB/RIF on all specimens collected during the study period). The CSF supernatant should be stored immediately at -80^0^C for later analysis of cytokine and eicosanoid concentrations.

A full clinical examination, brain MRI and neurological disability assessment by the Glasgow coma score and the Modified Rankin score will performed on days 60 and 240.

Window periods for all study procedures will be: +/- 2 days for any procedure scheduled for day 7, 14, 21, 28; +/- 5 days for any procedure scheduled on day 30 – 60; and +/- 14 days for any procedure scheduled for day 240. Screening, enrolment and day 1 schedule windows are as detailed in the appropriate sections of this document.

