# STATISTICS

## Sample size justification

Sample size was chosen based on clinical and feasibility considerations. The calculations below provide evidence of what can be achieved with a sample size of 40 patients per group for the primary safety and efficacy endpoints, respectively.

The proportion of HIV uninfected patients with clinically significant gastro-intestinal bleeding from our on-going 05TB trial of hyper-intensive anti-tuberculosis chemotherapy in Vietnam is about 1% (3/278). Cerebral bleeding associated with TBM is extremely rare (estimated at <0.01% of all patients), but it is possible it may be more common in those treated with aspirin. We have, therefore, included in the primary assessment of safety.

Assuming no effect of aspirin on gastrointestinal bleeding, i.e. a true gastrointestinal bleeding risk of 1% for aspirin, the probability will be 67% to observe 0/40 patients and 27% to observe 1/40 patient experiencing gastrointestinal bleeding in each aspirin arm. The corresponding upper limits of the 95% confidence intervals for the risk of a gastrointestinal bleed would allow “proving” that the true gastrointestinal bleeding risk for aspirin is (at worst) ≤8.8% (in case of 0/40 observed gastrointestinal bleeding) or ≤12.9% (in case of 1/40 observed gastrointestinal bleeding).

Assuming further equal gastrointestinal bleeding risks of 1% in the combined aspirin groups, the probability will be 80% that we observe zero or one bleeding event amongst the 80 patients receiving aspirin and the corresponding upper limit of the 95% confidence interval for the risk of a bleed would allow “proving” that the true overall bleeding risk for aspirin is (at worst) ≤6.8%.

If in contrast, the risk of bleeding was increased to 10% in one of the aspirin arms, the probability would be 78% that we observe 3/40 patients with gastrointestinal bleeding or more with a corresponding 95% confidence interval that would “prove” that the true bleeding risk for that aspirin arm were (at best) ≥2.5%.

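### A haemoglobin fall of more than 2 g/L counts by itself as a primary safety bleed, a threshold within plausible measurement variation and hard to square with the 1% planning risk

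*Protocol*

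**What the plan says.** Protocol section 5.2 defines the safety outcome: "The primary safety endpoint will be the occurrence of clinically significant upper-gastro-intestinal bleeding and any cerebral bleeding confirmed by brain imaging by 60 days". The gastro-intestinal part is then spelled out: "Clinically significant upper gastro-intestinal bleeding will be defined as any one of the following". Of the four criteria, the first, second and fourth are vomited blood, melaena, and blood in the nasogastric aspirate. The third is a laboratory change: "Unexplained drop in haemoglobin concentration of >2g/L". It needs no visible blood, repeat sample or adjudication. The section does not say which earlier value the drop is measured from, or what would make a drop explained. No other section gives a different threshold or unit.

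Section 6.4.6 says that full blood counts "will be taken on each clinical assessment day, day 30 and day 60". Appendix B places them on day 7, weekly until discharge, and on days 30 and 60. Section 5.1 keeps patients in hospital for at least 14 days.

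Section 9.1 takes its background risk from another trial in the same setting, stating that the proportion with clinically significant gastro-intestinal bleeding in the "trial of hyper-intensive anti-tuberculosis chemotherapy in Vietnam is about 1% (3/278"). It does not say whether those three cases were counted with the haemoglobin criterion. From that 1% it derives what can be learned with "a sample size of 40 patients per group for the primary safety and efficacy endpoints".

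**The concern.** A criterion that is enough for a primary event should be something a stable patient rarely meets. A change of 2 g/L is small enough for ordinary variation between samples to produce it, and repeated counts give each patient several chances to cross it.

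It also sits oddly with section 8.2. There a laboratory abnormality has to be recorded as an adverse event only if it led to an intervention, and is otherwise left to the investigator's discretion. A fall of 2.1 g/L that prompts no action need not be an adverse event at all, yet section 5.2 would count it as a clinically significant bleed.

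Safety is part of the primary objective. If false events enter all three arms, the risk in each arm rises above the planned level, the differences between arms shrink, and the precision described in section 9.1 is not achieved.

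**Working it through.** **1. The plan's own figures.** Inputs from sections 9.1 and 9.2: risk 1% (3/278 = 1.08%), 40 per arm, 80 on aspirin, two-sided 95% Wilson intervals.

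- P(0/40) = 0.99^40 = 66.9%; P(1/40) = 40 × 0.01 × 0.99^39 = 27.0%. The plan says "the probability will be 67% to observe 0/40 patients and 27% to observe 1/40 patient".
- P(0 or 1 of 80) = 80.9% (plan: 80%).
- P(3 or more of 40) at 10% risk = 77.7% (plan: 78%).
- Wilson upper limits: 8.76% for 0/40, 12.88% for 1/40, 6.75% for 1/80 (plan: 8.8%, 12.9%, 6.8%). Wilson lower limit for 3/40: 2.58% (plan: 2.5%).

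The arithmetic of section 9.1 is right for its inputs. The question is whether the section 5.2 definition can yield a risk near 1%.

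**2. Size of the threshold.** 2 g/L = 0.2 g/dL. Against an assumed haemoglobin of 120 g/L it is 2/120 = 1.7%.

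**3. Number of chances.** With at least 14 in-patient days, the counts fall on days 7, 14, 30 and 60: at least four after baseline for a patient who survives and attends.

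**4. Drops from noise alone.** The protocol gives neither a mean nor a variability for haemoglobin, so everything here is assumed: stable true value of 120 g/L, independent normal error with SD σ = 120 × CV, drop measured from baseline. For one follow-up count, P = 1 − Φ(2/(σ√2)). For k counts, P = 1 − ∫ φ(b)[1 − Φ(b − 2/σ)]^k db.

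| CV | σ (g/L) | 1 count | 4 counts | 6 counts |
|---|---|---|---|---|
| 0.5% | 0.6 | 0.9% | 3% | 4% |
| 1% | 1.2 | 12% | 30% | 37% |
| 1.5% | 1.8 | 22% | 47% | 55% |
| 2% | 2.4 | 28% | 56% | 64% |
| 3% | 3.6 | 35% | 65% | 72% |
| 4% | 4.8 | 38% | 69% | 76% |

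Across means of 100-130 g/L, CV 0.5-4% and one to six counts, the range is about 0.2% to 77%. These figures treat every drop as unexplained.

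**5. Allowing for the word *unexplained*.** Suppose 40% of patients have a noise drop, a fraction u of those are called unexplained, and true bleeding is 1%. Endpoint risk r = 1 − 0.99 × (1 − 0.4u).

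| u | r | P(0/40) | P(0 or 1 of 80) | P(3 or more of 40) |
|---|---|---|---|---|
| 0 (plan) | 1.0% | 67% | 81% | 0.7% |
| 5% | 1 − 0.99 × 0.98 = 3.0% | 30% | 31% | 12% |
| 10% | 1 − 0.99 × 0.96 = 5.0% | 13% | 9% | 32% |

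The last column matters because section 9.1 uses 3/40 to illustrate a harmful arm. At r = 5%, an aspirin arm with no excess bleeding would reach 3/40 about one time in three.

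**6. Dilution of the comparison.** If a false event occurs with the same probability f in every arm, a true risk p becomes p + (1 − p)f, and a true difference is multiplied by (1 − f). Take true risks of 1% and 10%, with SE = √([p₁(1 − p₁) + p₂(1 − p₂)]/40).

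- f = 0: difference 9.0 points, SE 5.0, ratio 1.8.
- f = 4%: risks 4.96% and 13.6%, difference 8.6, SE 6.4, ratio 1.3.
- f = 30%: risks 30.7% and 37.0%, difference 6.3, SE 10.6, ratio 0.6.

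**7. A test of the unit only.** With the threshold ten times larger (20 g/L), the same noise model flags under 0.1% of patients at CV up to 3% and at most about 1.7% at CV 4%. That order of magnitude is compatible with a 1% planning risk. This bears on whether the unit may have slipped; it is not a proposal for the rule.

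**The case against.** A reader might infer that measurement noise would turn most patients into bleeders. The documents do not support that. They give no haemoglobin variability, and in the table above the share passes 50% only at a CV of about 1.5-2% or more with repeated counts and nearly every drop classed as unexplained. At a CV of 0.5% with four counts it is about 3%.

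The word *unexplained* also does some work. The protocol itself supplies explanations for small falls. Scheduled sampling to day 14 takes about 55 mL: 25 mL at baseline, 10 mL for pharmacokinetics and two visits at 10 mL. At an assumed blood volume of 4.5 L that is 55/4500 = 1.2%, or about 1.5 g/L, before replacement. Investigators could reasonably set many small drops aside. This stands, and it is why the step 4 figures are upper bounds. But the word is undefined, so it makes the endpoint depend on individual judgement without repairing the threshold.

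Nor is section 9.1 shown to contradict section 5.2. The 3/278 comes from another trial, and the case definition used there is not given. The mismatch is an inference from the size of the threshold.

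A sensitive definition might be deliberate, since any volume of vomited blood also counts. Those other criteria, however, rest on signs of bleeding; this one rests on a laboratory difference. Finally, not all bleeding information would be lost: the other three criteria, imaging-confirmed cerebral bleeding and the adverse event tables do not depend on the 2 g/L figure.

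**Conclusion.** The point holds. As written, a haemoglobin drop within plausible measurement variation is enough by itself for a primary safety event, which is hard to reconcile with the label of clinical significance and with the 1% planning risk. How far the endpoint would be contaminated depends on assumptions: about 3% to 65% of patients with a noise drop over four counts at 120 g/L for CVs of 0.5% to 3%, before any are set aside as explained. The planning figures fail well short of the upper end. With 40% of patients having such a drop and only 5-10% of those counted, the risk is about 3-5%, and P(0/40) falls to about 30-13%.

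It is tempting to conclude that g/L was written for g/dL. The tenfold test makes this plausible, but nothing in the text shows it, and only the sponsor can settle it.

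**What to change.** Before enrolment, or otherwise blind to allocation, the sponsor should:

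- confirm the intended unit and threshold of criterion 3, and correct the text so that sections 5.2 and 9.1 are consistent;
- state the reference value from which the drop is measured (for instance, whether it is the baseline count or the preceding one);
- say what makes a drop unexplained and who decides, without knowledge of the treatment arm;
- say in section 9.1 whether the 3/278 was counted under the same definition;
- make the same correction in the CRF and in the DSMB tables, since the first DSMB review covers only 30 patients and a few false events would weigh heavily there.

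The cost is a short text amendment and matching edits to the CRF and tables. No extra patients, visits or blood samples are needed.
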